## Background

Type 2 diabetes mellitus (T2DM) is a substantial health problem with a high clinical and economic burden [1, 2]. Despite a recent prognostic improvement, coronary artery disease (CAD) remains one of the leading causes of mortality in people with T2DM [3]. CAD is often severe and silent in patients with T2DM [4], prompting screening in asymptomatic individuals. Previous randomised controlled trials (RCTs) have failed to provide evidence of the effectiveness of routine CAD screening in reducing major cardiovascular events and mortality in people with T2DM at moderate to high cardiovascular risk [5–9]. However, doubts remain about T2DM patients at a very high cardiovascular risk, who can benefit from this screening strategy, but in whom trials have not yet been conducted. Despite this lack of concrete evidence, current clinical practice and guidelines recommend routine CAD screening for silent CAD in individuals with diabetes at high cardiovascular risk [10]. The widespread practice CAD screening results in significant healthcare costs due to invasive testing, revascularisation procedures, and intensified pharmacological therapies. The cost-effectiveness of routine CAD screening has not been prospectively evaluated in T2DM people. Only two economic studies based on Markov models have addressed this issue by comparing screening versus no screening strategy in Japanese and American populations [11, 12]. The results of these studies were inherently limited by assumptions inherent in the models, uncertainties in the epidemiological and cost data, and variations in health care costs between countries.

In the midst of this discrepancy between the lack of tangible evidence and clinical practice, we are conducting the Cost-effectiveness of Screening of Coronary Artery disease in patients with type 2 DIABetes at a very high cardiovascular risk (SCADIAB) study to estimate the cost-effectiveness of routine CAD screening in T2DM patients with a very high cardiovascular risk.

### Study design

The study design and protocol have been published in a previous issue of this journal [13]. We report here updated methods and statistical approach that will be performed in this study, namely the emulation of a 2-arm randomised target trial using the French electronic health record (SNDS, *Système National des Données de Santé*), a claim database encompassing the whole French population [14, 15].

### Recruitment of participants and follow‑up

Data will be extracted from 1 January 2008 to 31 December 2019. The screening period will cover the 7 years from 1 January 2008 to 31 December 2014, which will allow us to identify patient eligibility criteria. All patients identified in the SNDS databases during the pre-selection period who met the inclusion criteria will be recruited in the study from 1 January 2015 to 31 December 2015. Participants will be followed for 4 years, until 31 December 2019 (Fig. 1).

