### Screening strategies and study allocation

Each patient will be assigned into one of the two study groups according to the CAD screening strategy performed during the recruitment period. Patients who had at least one CAD screening test will be assigned to the routine CAD screening group and included at the time of the first CAD test. Patients who did not perform any CAD screening (except for the resting electrocardiogram) will be assigned to the control group, and included at the time of the resting electrocardiogram, or at the time of a medical visit (general practitioner, diabetologist, or cardiologist), whichever comes first.

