### Eligibility criteria

The key inclusion criteria are patients aged 40 years or older, with T2DM for at least 7 years, two or more additional cardiovascular risk factors (obesity, hypertension, hypercholesterolemia, or tobacco smoking), and at least one microvascular or macrovascular disease: carotid stenosis, transient ischemic attack (TIA), stroke, lower-limb peripheral artery disease, chronic kidney disease (CKD), severe diabetic retinopathy requiring laser photocoagulation, or peripheral or autonomic diabetic neuropathy. The main exclusion criteria include the presence of CAD (a history of acute coronary syndrome, coronary revascularization, angina pectoris, or unstable angina), the performance of one or more CAD screening tests, or any visit to an emergency department for chest pain resulting for admission to a cardiac intensive care unit.

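### Eligibility is read from 2008–2014 data but the screening arm enters at its first CAD test in 2015, so event- or symptom-prompted tests can count as routine screening

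*Protocol article*

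**What the plan says.** All of this is in the protocol article.

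- **Recruitment of participants and follow-up.** The pre-selection period runs "from 1 January 2008 to 31 December 2014, which will allow us to identify patient eligibility criteria". Patients identified in that period "who met the inclusion criteria will be recruited in the study from 1 January 2015 to 31 December 2015". Data are extracted through 2019.
- **Screening strategies and study allocation.** Groups are formed "according to the CAD screening strategy performed during the recruitment period". For the screened group the rule reads: "Patients who had at least one CAD screening test will be assigned to the routine CAD screening group", with inclusion at the first such test. Patients with no test other than a resting ECG form the control group and are "included at the time of the resting electrocardiogram, or at the time of a medical visit", whichever is earlier.
- **Eligibility criteria.** The main exclusions are a history of acute coronary syndrome, coronary revascularisation, angina or unstable angina; a CAD screening test; and "any visit to an emergency department for chest pain resulting for admission to a cardiac intensive care unit". None of these carries a date.
- **Statistical analysis.** A high-dimensional propensity score with inverse probability weighting is to balance baseline characteristics. The date at which baseline is read is not given, and the reason for the test is not mentioned.

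**The concern.** A target trial emulation depends on eligibility, assignment and the start of follow-up coinciding. Here eligibility appears to close on 31 December 2014, while the screening arm starts on a date in 2015 that is itself set by a test. Tests cluster after coronary events and symptoms, so the interval before the test is when a patient is most likely to stop being the asymptomatic person whom the Background section has in mind.

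The two arms are not affected alike. Controls enter at a first visit or resting ECG, which symptoms need not trigger. Because allocation looks at the whole of 2015, a patient who becomes symptomatic and is tested is removed from the potential controls and placed in the screening arm.

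The primary outcome, cost per life-year gained, is exposed on both sides: such patients would be expected to cost more and to live less long. The main cardiovascular composite is exposed too, since it counts acute coronary syndrome and coronary revascularisation. Procedures that follow a diagnostic work-up would then be counted as consequences of screening.

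**Working it through.** The article states no sample size, event rate or effect size, so there is no figure of the plan's own to reproduce. The check is a reading of the text, some date arithmetic and an illustration on assumed inputs.

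**1. The gap.** Cut-off: 31 December 2014. Entry: 1 January to 31 December 2015. Shortest gap 1 day, longest 365 days. If entry were spread evenly over 2015 (an assumption), the mean would be (1 + 365)/2 = 183 days.

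**2. Which date governs the exclusions.** The exclusion for an earlier CAD test must stop before the qualifying 2015 test, or the screening arm would be empty. Some cut-off is therefore needed. The only one the article prints is the end of 2014; the alternative, the day before each patient's own test, is not stated.

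**3. Two readings side by side.**

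| Patient in 2015, before the index test | Exclusions stop at end of 2014 | Exclusions run to the test date |
|---|---|---|
| Acute coronary syndrome, revascularisation or coded angina | enters screening arm | excluded |
| Emergency visit for chest pain with cardiac intensive care admission | enters | excluded |
| Emergency visit for chest pain without that admission | enters | enters |
| Outpatient symptoms not coded as angina | enters | enters |

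The last two rows do not depend on the reading.

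**4. Possible share (assumed rates, not from the article).** Let r be the yearly rate of routine first tests and s the rate of event- or symptom-prompted first tests. The share of prompted tests is s/(s + r).
- s = 1%, r = 30%: 0.01/0.31 = 3.2%.
- s = 4%, r = 10%: 0.04/0.14 = 28.6%.

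**5. Possible bias (assumed inputs).** Let c be the misclassified share of the screening arm and h their event rate relative to the rest. If screening has no effect, controls are unaffected and weighting removes none of it, the observed ratio is 1 − c + c·h.
- c = 0.05, h = 1.5: 0.95 + 0.075 = 1.025.
- c = 0.10, h = 2: 0.90 + 0.20 = 1.10.
- c = 0.20, h = 3: 0.80 + 0.60 = 1.40.

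Reading h as a risk multiple, with an assumed 4-year mortality of 15%, the smallest and largest of these correspond to an excess of 15% × 0.025 = 0.4 and 15% × 0.40 = 6.0 percentage points. These figures show direction and possible scale, not an estimate.

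**The case against.** The best reply is that this is a short update and that the design was published in full earlier. Code lists and the claims definition of a screening test may be there, and the study-design figure, where such windows are usually drawn, is not shown. A history of CAD can also be read as history at inclusion, which is an individual date in 2015. On that reading the patient with an early-2015 infarction is excluded. Finally, a high-dimensional propensity score could take up some recent cardiac contacts and dispensings.

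Much of this stands, and it rules out several stronger statements that a reader might infer:

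- *That chest pain leading to intensive care is the only symptom exclusion.* Not supported: angina and unstable angina are excluded as well, and the list is presented as the main criteria, not all of them.
- *That covariates are fixed at the end of 2014, so weighting cannot see 2015.* Not supported: the article speaks only of baseline and does not date it.
- *That diagnostic tests are counted as screening.* The text shows that they can be, not that they are or how often.
- *That the exclusions certainly stop at the end of 2014.* This is the natural reading of the recruitment section, but not the only one.

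What the reply does not remove is the text in view. The article offers itself as the updated methods for the target trial, ties eligibility to 2008–2014, and sets time zero at a later test with no stated condition on indication. The rows of the table that hold on either reading are untouched by the dating argument. Weighting on covariates also does not mend an exposure group that mixes screening with diagnosis.

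**Conclusion.** The concern holds in a conditional form. Followed as written, the plan lets post-event tests enter the routine screening arm; on any reading of the dates, the criteria shown let some symptom-prompted tests enter it. Controls have no matching route, so the bias would tend to raise cost and events in the screening arm and make screening look worse on cost per life-year gained.

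The size cannot be derived from the article. The ratios of 1.025 to 1.40 rest wholly on assumed shares and risk multiples, with no contamination of controls and no benefit from weighting. The post-event part further assumes that the 2008–2014 window governs the undated exclusions. The symptom part assumes that no unshown document restricts index tests by indication. Because the weakness lies in how the exposure of the primary comparison is defined, it is more than a missing detail and should be settled before analysis.

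**What to change.** 1. In both arms, assess every exclusion and every baseline covariate up to the day before the participant's own time zero, and say so in the recruitment and eligibility sections.
2. Do not count as screening an index test done during an acute stay, or within a pre-specified look-back after a chest-pain or cardiac hospital or emergency contact or a new antianginal dispensing. Ninety days is an example of such a look-back; the article gives no basis for a particular length.
3. Apply the same look-back to controls at their time zero.
4. Vary the length in a sensitivity analysis, for instance 180 days.
5. State what becomes of a patient whose first 2015 test is discarded, so that such patients do not slip into the control arm by default.

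Cost: a change to the extraction rules. The 2015 claims already fall within the extracted period, so no new data are needed. The screening arm becomes somewhat smaller. A claims rule will still miss symptoms that left no trace in claims, and a control who enters early in the year cannot be checked at entry for symptoms that arise later, so the rule reduces the bias but does not abolish it.

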**Fig. 1 Fig1:**
[figure not shown]
Study design

### Screening strategies and study allocation

Each patient will be assigned into one of the two study groups according to the CAD screening strategy performed during the recruitment period. Patients who had at least one CAD screening test will be assigned to the routine CAD screening group and included at the time of the first CAD test. Patients who did not perform any CAD screening (except for the resting electrocardiogram) will be assigned to the control group, and included at the time of the resting electrocardiogram, or at the time of a medical visit (general practitioner, diabetologist, or cardiologist), whichever comes first.

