### Outcomes

The primary outcome is the incremental cost per life-year gained over 4 years in CAD routine screening group versus no screening in the perspective of French health insurance. The key secondary health economic endpoints include the cost-consequence analysis linking the total 4-year direct costs of each strategy and clinical endpoints; an analysis of budget impact for the French Insurance system to promote the routine CAD screening; and the total care consumption during follow-up. The key secondary clinical endpoints included the effects of CAD screening (versus no screening) in terms of major adverse cardiovascular events (a composite of acute coronary syndrome, coronary revascularization, or hospitalization for heart failure); all-cause mortality; major cerebrovascular events (a composite of stroke, hospitalization for TIA, or carotid revascularization); major adverse limb events (a composite of ischemic diabetic foot, lower-limb revascularization or amputation); and CKD or end-stage kidney disease (ESKD, requirement of any sustained haemodialysis or kidney transplantation). Each component of these composite endpoints will also be considered individually. Major cerebrovascular events, major adverse limb events and ESKD will be assessed during follow-up among participants without a baseline history of each condition (as appropriate). Finally, SCADIAB will also assess the frequency of routine CAD screening, expressed as the number of examinations performed yearly per individual.

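### Follow-up starts at a CAD test in any setting for screened patients but at the earliest ECG or visit for controls, so in-hospital entry can bias cost, survival and heart-failure results against screening

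*Protocol article*

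**What the plan says.** All references are to the Protocol article.

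- **Allocation** (Screening strategies and study allocation): patients are grouped "according to the CAD screening strategy performed during the recruitment period", which is the calendar year 2015.
- **Entry, screening arm** (same section): "assigned to the routine CAD screening group and included at the time of the first CAD test". Neither the care setting nor the reason for the test is stated.
- **Entry, control arm** (same section): "assigned to the control group, and included at the time of the resting electrocardiogram, or at the time of a medical visit", the visit being to a "general practitioner, diabetologist, or cardiologist), whichever comes first". No setting is stated for the ECG either.
- **Exclusions** (Eligibility criteria): known CAD, defined as "a history of acute coronary syndrome, coronary revascularization, angina pectoris, or unstable angina"; a CAD screening test; and "any visit to an emergency department for chest pain resulting for admission to a cardiac intensive care unit". Heart failure is not listed, nor are admissions for other causes. Stroke, limb artery disease and kidney disease are among the qualifying conditions.
- **Eligibility look-back** (Recruitment of participants and follow-up): it closes on 31 December 2014, before the recruitment year.
- **Outcomes** (Outcomes): the primary outcome is incremental cost per life-year gained over 4 years. A secondary analysis is described as "linking the total 4-year direct costs of each strategy and clinical endpoints". Heart-failure hospitalisation is a MACE component. Only the cerebrovascular, limb and ESKD outcomes are restricted to patients free of the condition at baseline.
- **Adjustment** (Statistical analysis): a high-dimensional propensity score on baseline characteristics, applied through IPTW.

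**The concern.** The two arms start their clocks at different kinds of contact. A CAD test may be done during an admission for a foot ulcer, a stroke, an infection or new heart failure. Under the stated rule, time zero then lies inside that stay. A control's time zero is the first of several routine contacts in the year, so it will more often be ambulatory.

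Entry during an unplanned stay puts the patient at a moment of high cost and high short-term risk that screening did not cause. If this happens more often in the screening arm, both parts of the primary ratio move the same way: incremental cost rises and life-years gained fall. Heart-failure events can move with them. Aligning the calendar dates of time zero would not remove this, because the difference lies in the patient's state at entry.

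**Working it through.** The article gives no cost, mortality, event count or in-hospital share, so there is no figure of its own to reproduce. The check has two parts.

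**1. Following the rule.** Take two alike patients. Each sees a GP in January 2015 and is admitted for heart failure in June 2015.
- Patient A has a CAD test during the stay. A is allocated to screening, with time zero in June, inside the admission.
- Patient B is not tested. B is allocated to control, with time zero in January.

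None of the listed exclusions removes A: the admission is not the chest-pain route, heart failure is not listed, and June 2015 falls after the look-back closes. B's stay is still counted, five months into B's follow-up. The asymmetry is therefore not that controls have no stays. It is that some of the screening arm is selected at the moment of a stay, which comes on top of whatever admissions the next 4 years bring.

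**2. Size, on assumptions only.** Let
- f and g be the shares of screened and control patients whose time zero falls in a hospital stay;
- C be the cost of that stay, assumed EUR 3,000 to 6,000;
- m be the excess early mortality, assumed 2% to 10%;
- 3.6 be the assumed life-years lost within the 4-year horizon per early death.

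Spurious cost difference per patient = (f − g) × C. Spurious life-year difference = −(f − g) × m × 3.6.

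Cost with g = 0:
- f = 5%: 0.05 × 3,000 = EUR 150
- f = 10%: 0.10 × 3,000 = EUR 300; 0.10 × 6,000 = EUR 600
- f = 20%: 0.20 × 6,000 = EUR 1,200

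Cost with g above 0:
- f = 20%, g = 2%: 0.18 × 3,000 = EUR 540; 0.18 × 6,000 = EUR 1,080. With equal arm sizes, 0.20 / 0.22 = 91% of index stays are in the screening arm.
- f = g = 5%: EUR 0, with 50% of index stays in each arm.

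Life-years:
- f = 5%, g = 0, m = 2%: −0.05 × 0.02 × 3.6 = −0.0036
- f = 20%, g = 0, m = 10%: −0.20 × 0.10 × 3.6 = −0.072
- f = 20%, g = 2%: −0.013 (m = 2%) to −0.065 (m = 10%)

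**How large g might be.** An in-hospital ECG sets a control's time zero only if it precedes every eligible visit in 2015. Assume 0.3 admissions per year and a mean wait of 0.5 to 1.5 months to the first visit. Then g is at most about 0.3 × 0.5/12 = 1.25% to 0.3 × 1.5/12 = 3.75%. With f = 5% and g = 3.75% the cost difference is only 0.0125 × 3,000 = EUR 38 to 0.0125 × 6,000 = EUR 75.

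The direction is fixed whenever f > g. The size depends on two shares that the document does not give.

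**The case against.** The strongest reply is that the article is silent on setting rather than permissive. It speaks of routine screening, its Background frames screening as done in asymptomatic people, and a test prompted by new heart failure would be diagnostic on that view. Eligibility criteria gives only key and main criteria, and Study design points to a separately published protocol, so a restriction may exist elsewhere. That is fair as to what the full protocol may contain. It does not change the entry rule printed here, which gives the arms different index contacts, in an article presented as the updated methods for the target-trial emulation.

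Several stronger readings are tempting, and the document does not support them:
- *Index stays fall almost only on the screening arm, and a control can hardly be in hospital at entry.* No in-hospital share is given, and a control's ECG may be done in hospital.
- *Controls escape the cost of such stays.* They bear every untested admission after entry.
- *The whole index stay is charged to screening, or a heart-failure stay counts as a MACE on day 0.* The article does not say whether a stay under way at time zero is baseline or follow-up. If it is baseline, only the costly and risky weeks after it remain at issue.
- *Weighting cannot balance this.* A high-dimensional score could include recent admissions. It would help if hospital status at time zero were a covariate and comparable hospitalised controls existed; neither is established.
- *The artefact exceeds the cost of the test itself.* No test cost is given.

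One more part of the reply stands. Some screening may be done during a stay planned for it, and that stay is then a genuine cost of the strategy. Barring every in-hospital test from the main analysis would remove real screening cost and change the population.

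**Conclusion.** The concern holds in a limited form. The stated entry rule uses different kinds of contact in the two arms, and the listed exclusions leave room for a test during an unplanned admission to set time zero. In-hospital entry is therefore likely to be commoner in the screening arm. Whenever it is, the bias in 4-year cost, life-years and heart-failure hospitalisation runs against screening.

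The EUR 150 to 1,200 per screened patient is an illustration, not an estimate. It is an upper-end range because it sets the control share to zero and charges the full cost of the stay. It shrinks to 0 as the two shares become equal. The life-year figures rest on the assumed early mortality in the same way. The matter should be settled before the analysis because it touches both parts of the primary ratio and can be resolved from dates.

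**What to change.** - Apply one rule to both arms: time zero may not fall within an unplanned hospital stay, or within a short window after discharge whose length is set in advance. State what happens to a patient whose first qualifying contact is barred, and handle it alike in both arms.
- Keep tests done during stays planned for screening or diabetes assessment, together with the cost of those stays.
- State that the cost and diagnoses of an unplanned stay that began before time zero are not counted as outcomes.
- Include recent-admission status at time zero in the propensity score.
- Report the in-hospital share at time zero in each arm, so that the size of the problem can be seen.
- As sensitivity analyses, repeat the primary analysis with all in-hospital tests included and with all excluded.

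The cost is small: a date rule on the claims data, a definition of an unplanned stay, and two further runs. The downside is that some screened patients leave the main analysis, which narrows the population to which its result applies.

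### The 4-year cost window opens on the CAD test for screened patients but on the first resting ECG or medical visit for controls, so the two cost totals are not aligned

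*Protocol article*

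**What the plan says.** The section on screening strategies and study allocation assigns patients "according to the CAD screening strategy performed during the recruitment period". A patient with at least one test is "assigned to the routine CAD screening group and included at the time of the first CAD test". A patient without one is "included at the time of the resting electrocardiogram, or at the time of a medical visit (general practitioner, diabetologist, or cardiologist), whichever comes first".

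The section on recruitment and follow-up says that eligible patients "will be recruited in the study from 1 January 2015 to 31 December 2015" and adds: "Participants will be followed for 4 years, until 31 December 2019".

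Under Outcomes: "The primary outcome is the incremental cost per life-year gained over 4 years in CAD routine screening group versus no screening", from the French health insurance perspective. A secondary endpoint is "the cost-consequence analysis linking the total 4-year direct costs of each strategy and clinical endpoints". Total care consumption during follow-up is also listed.

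The Statistical analysis section plans a high-dimensional propensity score and inverse probability of treatment weighting to balance baseline characteristics. The study is presented as the emulation of a two-arm randomised trial, and its primary effect is that of being assigned to a strategy at inclusion.

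**The concern.** In the trial being emulated, a patient would be assigned to screening or no screening at some contact with the health service, and the test would follow. Costs in both arms would run from that contact. Under the article's rule, a screened patient's clock starts when the strategy has already been carried out, whereas a control's clock starts at an ordinary consultation or ECG.

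This has two consequences for the numerator of the primary ratio. A consultation or ECG that led to the test on an earlier day is lost from the screening arm, while a paid contact is guaranteed on day 0 of every control. In the other direction, a test performed during a hospital stay could bring the cost of that stay to day 0 of the screening arm, with no counterpart among controls. Both are systematic, so a larger sample does not remove them. They feed directly into an incremental cost that is then divided by a life-year difference, and the budget impact analysis could inherit them.

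**Working it through.** **1. The two rules side by side**

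| | Screening arm | Control arm |
|---|---|---|
| Event that opens follow-up | First CAD test in 2015 | First resting ECG or medical visit in 2015 |
| Contact that led to the test, if on an earlier day | Before day 0, outside the window | Not applicable |
| Consultation or ECG on day 0 | Not guaranteed | Guaranteed |
| CAD test on day 0 | Guaranteed | None |
| Horizon | 4 years | 4 years |

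The misalignment is therefore in the stated rule. It does not depend on any detail that the article leaves out.

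**2. Can the planned adjustment repair it?** Inverse probability weights make the patients in the two arms alike in measured baseline characteristics. They do not change which event opens each patient's window. Two identical patients, one in each arm, would still have cost totals that begin on different kinds of event.

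**3. Illustration of the timing.** The article gives no visit rates, so these are assumptions: visits follow a Poisson process at r = 4, 8 or 12 per year, and test dates are uniform over 2015 (mean 6 months).

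Mean control entry, given at least one visit, in years: m = [1/r − (1 + 1/r)e^(−r)] / (1 − e^(−r)).

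- r = 4: 12m = 2.78 months; gap to screened entry 6 − 2.78 = 3.22 months; 4 × 0.5 = 2 visits in 2015 before the test.
- r = 8: 1.50 months; gap 4.50; 4 visits.
- r = 12: 1.00 month; gap 5.00; 6 visits.

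These 2 to 6 earlier visits are not all a net loss, because each arm is still followed for 4 years. What changes the cost difference is the day-0 contact that controls have and screened patients lack, plus any further contact that occurred because of the test. One contact is 1/(4r) of all visits over 4 years: 1/16 = 6.25%, 1/32 = 3.1% and 1/48 = 2.1% for the three rates.

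**4. Illustration of the cost error.** Again, every input is assumed.

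- Contacts missing from the screening arm: v × c, with v = 1 to 3 contacts at c = 25 to 50 cost units. This gives 1 × 25 = 25 to 3 × 50 = 150 units per patient, understating the cost of screening.
- Index hospital stays: p × S, with a share p = 5% to 40% of index tests done in a stay costing S = 1,000 to 5,000 units. The stay is counted in full and would have happened anyway. This gives 0.05 × 1,000 = 50 to 0.40 × 5,000 = 2,000 units per patient, overstating the cost of screening.
- Net error pS − vc: from 50 − 150 = −100 to 2,000 − 25 = +1,975 units per screened patient. If no index test was done in a stay, or a costing rule removes the stay, only the first term remains, −25 to −150.

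The sign changes within the assumed range.

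**5. Passage into the ratio.** For a given life-year gain, the shift in the ratio is the net error divided by that gain. The article gives no expected gain. With an assumed 0.01 to 0.05 life-years over 4 years, a net error of −100 units shifts the ratio by −100/0.05 = −2,000 to −100/0.01 = −10,000 units per life-year. This shows only how the division magnifies a fixed error; it does not predict the trial's error.

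**The case against.** The strongest reply is that this is a condensed article that refers to a previously published protocol. Costing rules for the index day, and for a stay that contains the test, are the kind of detail it may leave elsewhere. The eligibility section lists only main exclusions, so its silence on inpatient tests does not show that they qualify. A reader might infer that index hospital stays are charged to screening. The documents do not say so, and the statement can only be conditional.

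Second, a target trial normally counts costs from assignment, so visits before assignment are properly outside the window. In patients with long-standing, complicated diabetes, many such visits would have happened under either strategy. A reader might infer that the whole cost of ordering the test is lost. That would need an ordering visit on an earlier day, no costed look-back, and a visit that was additional. The first two are the natural reading but are not written, and the third is unknown.

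Third, both effects follow from the choice of time zero, so this should not be counted again as a separate allocation defect.

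All three limit the size of the point. None removes its basis: the entry rule differs by arm, and the 4-year outcome runs from entry. A costing rule held elsewhere would have to override that stated rule.

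The simplest repairs also need care. Adding a pre-test costing window to the screening arm alone would give that arm a longer window and bring in unrelated visits. Moving both arms to a visit while still allocating by later testing would add immortal time for screened patients, who must survive from visit to test. Anchoring on the test avoids that in the screened arm.

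**Conclusion.** The concern holds as a misalignment of time zero that affects the cost windows. The plan opens the window on different care events by arm, and baseline weighting does not correct this. The conclusion assumes that costs accrue from each patient's inclusion date, which is the natural reading of a 4-year follow-up and a 4-year cost outcome.

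The size and net direction of the error cannot be determined from the document. It gives no unit costs, no share of tests done in hospital, no cost difference and no life-year gain. A reader might infer that the ratio is biased in favour of screening, or against it, by a stated amount; neither is supported. The missing-contact effect alone is likely to be modest, at one to a few contacts over 4 years. The hospital-stay effect could be larger, but it rests on two conditions that the article does not settle: that such tests qualify as index tests, and that the stay is costed in full.

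It is a point that should be changed before analysis, because the primary outcome depends on it and the change needs no new data.

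**What to change.** - Define time zero in both arms as the same type of qualifying contact in 2015 (medical visit or resting ECG), with eligibility checked at that date. Costs and life-years both run for 4 years from it. Even an entry on 31 December 2015 leaves 4 years to the end of the extract.
- Assign strategy from testing within a fixed, prespecified grace period after time zero. Handle the resulting immortal time explicitly, for example by cloning, censoring and weighting, or by sequential emulated trials. Without this step the common anchor replaces a cost error with a survival error.
- State one rule for costs on the index date and apply it to both arms.
- Report the cost per life-year in two sensitivity analyses: one excluding patients whose index test was done in a hospital stay, and one using the currently planned test-date anchor. The exclusion affects one arm only, so it belongs in a sensitivity analysis and not in the main result.
- Do not add a pre-test costing window to the screening arm alone.

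The cost is additional programming and analysis on data already extracted, and a short addition to the analysis and costing plan. The length of the grace period is a convention, so a second length should be shown.
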